#### 8.3.2 Criteria for non-inclusion of patients

- Patients with metastatic cancer

- Patient with a primary cancer other than breast cancer
- Patients with a history of neurological damage
- Patient with treated sleep apnea syndrome
- Patient with drug or alcohol abuse ( $\geq 3$  drinks/day on average and/or  $> 10$  drinks/week)
- Patient with treatment that has not been stabilized for at least 3 months (hypnotics, antidepressants, anxiolytics)
- Patient with a personality disorder or progressive psychiatric pathology
- Patients with contraindications to MRI (claustrophobia; metallic objects in the body such as pacemakers, implanted equipment activated by an electrical, magnetic or mechanical system, hemostatic clips for intracerebral aneurysms or carotid arteries, orthopedic implants)
- Patient with uncorrected vision problem
- Patients with pre-existing cognitive impairment at the time of cancer diagnosis

### 8.3.3 Selection criteria for cancer-free women

- Female from general population matched for age and education (Barbizet scale) to female patients
- Female, minimum education level 3 "end of primary education" (Barbizet scale)
- French-speaking woman
- Woman who signed consent to participate in the study
- Woman with no history of cancer
- Woman with sleep complaints (ISI  $> 7$ )
- Woman without treated sleep apnea
- Woman with access to the Internet from a computer at home
- Woman who does not work shifts
- Woman with no history of neurological damage
- Woman with no drug use or alcohol abuse ( $\leq 3$  drinks/day on average and/or  $< 10$  drinks/week)
- Woman with no treatment that has not been stabilized for at least 3 months (hypnotics, antidepressants, anxiolytics)
- Woman with no personality disorder or progressive psychiatric pathology
- Woman with no contraindications to MRI (claustrophobia; metal objects in the body such as pacemakers, implanted equipment activated by an electrical, magnetic or mechanical system, hemostatic clips for intracerebral aneurysms or carotid arteries, orthopedic implants).
- Woman with no uncorrected vision problems

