## 5 SCIENTIFIC CONTEXT OF THE STUDY

About 40% of patients treated for breast cancer frequently complain of sleep disorders. Insomnia is the most frequent one. The prevalence of insomnia complaints is higher in breast cancer patients than in other types of cancer, and is also higher than in the general population (between 20% and 70% in breast cancer patients vs. 30% in the general population) . A recent study indicates that sleep complaints concern 25% of patients even before diagnosis, and 46% (including 18% complaining of insomnia) at the time of diagnosis, showing the negative impact of the announcement of the pathology on subjective sleep quality, and in particular on symptoms suggestive of insomnia . However, objective evidence of sleep patterns's modifications in breast cancer remains scarce and inconclusive (see  for review). In particular, previous studies have focused only on the effects of chemotherapy and have not always included a control group, limiting the scope of their results. The links with cognitive and psychopathological processes, as well as the underlying mechanisms, are not clearly demonstrated in this pathology. Finally, taking into account patients' complaints, it seems necessary to limit sleep disorders in breast cancer in order to improve patients' quality of life using non-medicinal, easy-to-implement approaches.

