#### 5.5 SECONDARY OBJECTIVES

##### Axis 1:

- 1)
  - a) To assess the effects of cancer and chemotherapy on sleep and circadian rhythms
  - b) To determine whether the presence of sleep disorders is associated with altered circadian rhythms
- 2) To assess the effects of cancer and chemotherapy on cognitive abilities and their neuro-functional correlates
- 3) To assess the effects of cancer and chemotherapy on cortical structure
- 4) To assess the effects of cancer and chemotherapy on functional connectivity at rest
- 5) To evaluate the link between sleep disorders and:
  - a) Cognitive abilities and their neuroanatomical correlates
  - b) The stress-related physiological systems
  - c) Quality of life

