## 6 RESEARCH HYPOTHESIS AND EXPECTED RESULTS

##### Axis 1:

- 1)
  - a) Sleep and circadian rhythms would be altered in patients before chemotherapy compared with cancer-free subjects. Chemotherapy would exacerbate these effects compared with the no-chemotherapy group
    - For sleep, more awakenings lasting more than a minute and poorer sleep quality are expected.

- For circadian rhythms, the sleep/wake and cortisol rhythms are expected to be less ample.
- b) Altered rhythms have deleterious effects on sleep quality**
- 2)** Cognitive abilities would be more impaired after than before chemotherapy, whereas no decline is expected in patients not treated with chemotherapy and in healthy subjects. More specifically, this decline is expected to affect:
    - Spatial and episodic memory
    - Working memory
    - Executive and attentional functions
    - Functional connectivity during the ANT (Attentional Network Test) task, particularly within the orientation and cognitive control networks
  - 3)** After chemotherapy, the cortical structure should be altered, particularly in the regions involved in the above-mentioned cognitive abilities (i.e., hippocampus, frontal regions, cerebellum) compared to before chemotherapy, and compared to patients not treated with chemotherapy and healthy subjects.
  - 4)** For both groups of patients, the dynamics of functional connectivity at rest prior to chemotherapy should be altered, with greater ruminations than in the healthy group.
  - 5) a)** Sleep disturbances (independently of the effects of anxiety and depression) are thought to be linked to cognitive abilities and their neuro-anatomical correlates, specifically:
    - Episodic and spatial memory performance
    - White matter structure and functional connectivity
  - b)** Sleep disturbances are also associated with hyperactivity of physiological stress systems
  - c)** Sleep disturbances are associated with a lower quality of life

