#### 8.3.1 Patient inclusion criteria

- Patient aged 45 to 65
- Patient with localized breast cancer, whether or not to start adjuvant chemotherapy
- Patient with education level 3 "end of primary education" (Barbizet scale)
- Patient fluent in French
- Patient having signed consent to participate in the study
- Patient with sleep complaints (ISI > 7)
- Patient with access to the Internet from a home computer

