### 8.4.3 Inclusion report

Participants who have signed their consent to participate will be asked to perform the following tests:

- ISI (sleep complaints)
- Berlin questionnaire (sleep apnea)

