### 12.2 STATISTICAL ANALYSIS

**Axis 1:** In order to characterize the sleep of breast cancer patients before and after adjuvant chemotherapy, sleep parameters measured by polysomnography (in particular sleep efficiency and number of awakenings) or by questionnaire will be described in terms of headcount for qualitative variables, and mean and standard deviation (or median and range) for quantitative variables, at T1 and T2 in each of the groups of interest. Similarly, circadian rhythm parameters measured by actigraphy (e.g. mean amplitude over a week) or by salivary cortisol assay will be described at each time and by group. To assess the effect of cancer on sleep and circadian rhythm, parameters at T1 and T2 will be compared between patients and controls using a Chi test or a Student (or Wilcoxon) test. To assess the effect of chemotherapy on sleep and circadian rhythm, the parameters of chemotherapy-treated patients will be compared between T1 and T2 by a McNemar test or a Student (or Wilcoxon) test for paired series. Alternatively, the effect of chemotherapy on T2 parameters can be tested in linear or logistic models adjusted for T1 parameters. Relationships between sleep parameters and circadian rhythm parameters will be assessed using a correlation matrix (Pearson's or Spearman's). The relationship between sleep parameters and scores on cognitive tests and quality-of-life assessments can be assessed at any time using a linear mixed model (taking into account correlation between repeated measures of the same subject).

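### ISI > 7 is required of patients and controls alike, so the patient-control comparison estimates a difference among women with sleep complaints, not the unrestricted cancer effect the protocol names

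*Protocol*

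**What the plan says.** The patient list (8.3.1) includes "Patient with sleep complaints (ISI > 7"). The list for cancer-free women (8.3.3) includes "Woman with sleep complaints" with the same cut-off. The synopsis repeats both. The ISI is given at the inclusion work-up (8.4.3), before T1.

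The claims built on these groups carry no such restriction. Objective 1a in 5.5 reads "To assess the effects of cancer and chemotherapy on sleep and circadian rhythms". The hypothesis in section 6 is "Sleep and circadian rhythms would be altered in patients before chemotherapy compared with cancer-free subjects". Section 12.2 gives the analysis: "To assess the effect of cancer on sleep and circadian rhythm, parameters at T1 and T2 will be compared between patients and controls". ISI and PSQI scores are among the measures for objective 1a (7.2, Table 2). The primary Axis 1 endpoints are polysomnographic sleep efficiency and awakenings (7.1).

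On prevalence, section 5 gives insomnia complaints as "between 20% and 70% in breast cancer patients vs. 30% in the general population". It adds, from another study, that 46% had sleep complaints at diagnosis, of whom some (18% overall) complained of insomnia.

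**The concern.** Both groups are selected on a measure of the outcome under study, and the difference between them is then named as what cancer does to sleep. The hypothesis speaks of cancer-free women in general, but the trial samples only those with a complaint. Section 5.1 relies on the control group to separate changes due to cancer from changes due to treatment, so the label matters.

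If complaints are commoner in patients, one cut-off takes a more extreme slice of the control population than of the patient population. Part of any true difference is then removed at entry. This is plainest for ISI, which serves as both entry criterion and outcome. The same selection carries into the T2 patient-control comparison, to the extent that T2 measures correlate with the inclusion ISI.

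**Working it through.** The protocol makes no power calculation (12.1) and states no effect size, so there is no figure of its own to reproduce. The check concerns the direction and size of the selection effect.

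**Inputs.** Prevalence 30% in the general population and 46% in patients (section 5), used as stand-ins for the proportion with ISI > 7. Assumed, not in the protocol: normally distributed complaint severity with equal SD in the two groups; a true polysomnography difference of 0.40 SD (patients worse); and a within-group correlation r between ISI and the polysomnography endpoint. SD units are those of the unselected populations.

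**Step 1, ISI before selection.** The common cut-off lies at z(0.70) = 0.524 in controls and z(0.54) = 0.100 in patients. The underlying shift is 0.524 − 0.100 = 0.424 SD.

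**Step 2, ISI after selection.** The mean above a cut-off c exceeds the group mean by φ(c)/(1 − Φ(c)).
- Controls: 0.348/0.30 = 1.159.
- Patients: 0.397/0.46 = 0.863, giving a mean of 0.424 + 0.863 = 1.287.
- Difference: 1.287 − 1.159 = 0.128 SD, about 30% of 0.424.

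This treats the T1 ISI as equal to the inclusion ISI. If the two correlated at 0.7 (assumed), the T1 contrast would be 0.424 − 0.7 × 0.296 = 0.217 SD: still compressed, but less so.

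**Step 3, polysomnography.** Observed difference = true difference − r × (control shift − patient shift) = 0.40 − r × (1.159 − 0.863) = 0.40 − 0.296r. A simulation with 2 million women per group before selection, run with a true difference of 0.424 SD, gave 0.361, 0.333 and 0.277 at r = 0.2, 0.3 and 0.5. The formula gives 0.365, 0.335 and 0.276.

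**Step 4, other prevalences quoted in section 5.** Controls stay at 30%.

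| Patients | Shift gap | ISI before → after (SD) | Polysomnography, true 0.40 SD, at r = 0 / 0.2 / 0.3 / 0.5 |
|---|---|---|---|
| 46% | 0.296 | 0.42 → 0.13 | 0.40 / 0.34 / 0.31 / 0.25 |
| 40% | 0.193 | 0.27 → 0.08 | 0.40 / 0.36 / 0.34 / 0.30 |
| 70% | 0.662 | 1.05 → 0.39 | 0.40 / 0.27 / 0.20 / 0.07 |
| 20% | −0.241 | −0.32 → −0.08 | 0.40 / 0.45 / 0.47 / 0.52 |

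At 20% the ISI contrast still shrinks toward zero, but the polysomnography difference is enlarged.

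**Step 5, criterion removed for controls only.** The control shift becomes zero. The ISI contrast is then 0.424 + 0.863 = 1.287 SD against a true 0.424. Polysomnography becomes 0.40 + 0.863r = 0.57, 0.66 and 0.83 SD at r = 0.2, 0.3 and 0.5. The largest error is 0.43 SD, against 0.15 SD when both groups are selected.

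**The case against.** The main Axis 1 objective (5.4) is to characterise sleep in comparison with the other groups, and 12.1 calls the study descriptive and exploratory. Comparing women who have complaints, with and without cancer, is a legitimate question, and the entry rule suits Axis 2, where women receive stimulation. This stands. A reader might infer that the comparison is uninformative, and it is not. But neither the exploratory label nor Axis 2 narrows objective 1a, its directional hypothesis or the analysis sentence in 12.2.

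A reader might also infer that the pull toward no difference is established. The documents do not support that. The 46% covers all sleep complaints and the 30% insomnia complaints, from different sources. Neither is a rate of ISI > 7, and neither is specific to women aged 45 to 65 about 1.5 months after surgery. Section 5 does say overall that complaints are commoner in breast cancer, which makes attenuation the likelier direction, but its own range starts at 20%.

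Nor should the roughly 70% loss on ISI be carried over to the primary endpoints. There the 46% scenario gives a loss of 15% to 38% of a true 0.40 SD at the assumed correlations (0.06/0.40 to 0.15/0.40), and none at zero correlation. Finally, nothing in the protocol says that a null result would be read as showing that cancer leaves sleep unaltered. That risk follows from the wording and is not a stated plan.

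**Conclusion.** The point holds as a mismatch between who is sampled and what is claimed. Following the protocol as written gives a contrast among women with ISI > 7, labelled as the cancer effect in general. This conclusion rests on the text alone and needs no model.

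The sizes do need one. With 30% and 46% as stand-ins, ISI falls from 0.42 to 0.13 SD. The polysomnography figures are conditional on a correlation the protocol does not give, and their direction is conditional on complaints being commoner in patients. A reader might conclude that freeing controls from the criterion would be the stronger design. With patients still selected, that overstates the difference by more than the present rule distorts it. The within-patient T1 to T2 comparison is not affected by this patient-control selection.

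**What to change.** - Restate objective 1a (5.5 and synopsis), its hypothesis (section 6), and the cancer-effect analysis (12.2) and conclusion as applying to women with sleep complaints, ISI > 7.
- Do not use T1 patient-control tests of ISI as evidence on the effect of cancer. Present ISI, and PSQI as a related self-report, descriptively with the selection stated.
- Where the screening ISI of consenting women who were not included is available, report it. Under 8.4.1.1 the study is offered to patients who already meet the criteria, so referral may have filtered for complaints, and these values need not show the full extent of selection.
- Do not remove the criterion for controls alone.

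The cost is mainly rewording and a narrower claim. Keeping screening values may need a small data provision, because 8.4.1 records inclusion only after the criteria have been checked.

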## 8.4 COURSE OF THE STUDY

### 8.4.1 Inclusion procedure

#### 8.4.1.1 Patient inclusion

The study will be proposed by oncologists and/or radiotherapists to patients meeting the eligibility criteria (groups with and without adjuvant chemotherapy). Patients will be given an information note and an informed consent form. They will have a cooling-off period of the duration of their choice.

Once the patient's agreement has been obtained by signing the study consent form, the selection criteria will be verified before inclusion in the trial.

Study-specific examinations requested prior to inclusion (inclusion work-up) will be carried out after consent has been signed and prior to inclusion.

Inclusion will be recorded on the study software via an Internet portal.

An identification number will be assigned to the patient and used throughout the study.

#### **8.4.1.2 Inclusion of cancer-free women**

Healthy volunteers will be recruited through acquaintances, associations, the “Espace Rencontre et Information [ERI]” at the Centre François Baclesse, or other groups of individuals. After prior phone contact and a brief presentation of the study, healthy volunteers will be invited to our research unit for the inclusion visit. During this visit, the investigator will present the purpose and modalities of the study, and then give the volunteers an information leaflet and a consent form. Control participants will be given a period of reflection of their choice to decide whether or not to participate in the protocol.

Cancer-free women will be matched in age and education (Barbizet scale) to patients.

After written agreement from the subject, verification of all selection criteria, and before starting the study, inclusion will be recorded on the study software via an Internet portal.

An identification number will be assigned to the volunteer woman, to be used throughout the study.

#### **8.4.2 Study evaluations**

A table summarizing the investigations requested and a diagram showing the different stages in the evaluation of participants are included at the beginning of the document (*Figure 1*).

The first evaluation will be carried out within one month of inclusion and before the start of chemotherapy (CHI group) or radiotherapy (NCH group), depending on the availability of participants.

Throughout the evaluation sessions, participants will be accompanied by the UMR 1077 team, comprising a neuropsychologist, a sleep technician and a PhD student.

Prior to the assessment sessions, actigraphy data will be collected from participants 2 weeks before each assessment session (T1, T2 and T3). For this purpose, an actigraph and a sleep diary with explanations on how to use them will be provided to participants either *in person*, or remotely (actigraph and sleep diary sent by post and videoconference).

The assessments proposed to the participants during the different study phases (T1, T2 and T3) are presented in the following figures (*Figure 2* and *Figure 3*). Each evaluation sequence will be carried out over 2 half-days (afternoon and morning), separated by a night's sleep to allow polysomnography examination.

[figure not shown]

**Figure 2.** Assessments offered to participants at T1 and T2

**Note.** Actigraphy will be provided 2 weeks before T1, idem at T2; At T1, a preliminary interview will take place at the reception of the participants (approximately 30 min, in addition to the MRI instructions); At T1, a period of familiarization with the galvanic vestibular stimulation equipment will take place before the MRI examination (20 min); PSG:

[figure not shown]

**Figure 3.** Assessments offered to participants at T3

**Note.** Actigraphy will be provided 2 weeks before T3; PSG: Polysomnography

### 8.4.3 Inclusion report

Participants who have signed their consent to participate will be asked to perform the following tests:

- ISI (sleep complaints)
- Berlin questionnaire (sleep apnea)

#### 8.4.4 T1 and T2 reports

##### **In patients treated with adjuvant chemotherapy (CHI group)**

- The T1 assessment will take place after surgery and before the start of chemotherapy.
- The T2 assessment will take place 2 weeks after the end of the last session of chemotherapy.

##### **In patients not treated with adjuvant chemotherapy (NCH group)**

- The T1 assessment will take place after surgery and before the start of radiotherapy.
- T2 assessment will take place 6 months after T1

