## **7 JUDGING CRITERIA**

### **7.1 MAIN CRITERION**

**Axis 1:** The primary endpoint is sleep efficiency (ratio of total sleep time to time spent in bed) and the number of awakenings lasting more than one minute. These data are derived from polysomnography.

**Axis 2:** The main criterion selected are amplitude (corresponding to half the maximum variation in the rhythm under consideration) and acrophase (i.e. the time of day when activity or cortisol is highest). Changes in sleep/wake rhythms will be quantified over the 2-week

intervention period, and will be derived from actigraphy. Changes in cortisol rhythm will be measured using saliva samples obtained at T2 and T3.

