## 8 STUDY PLAN

### 8.1 METHODOLOGY

The ICANSLEEP project is a bicentric longitudinal study.

Data from 25 patients with localized breast cancer treated with chemotherapy will be compared with those from a group of 25 patients not treated with chemotherapy and a group of 25 cancer-free volunteers (control groups), matched for sex, age and years of education (Barbizet scale).

The various evaluations will be carried out as follows:

- At T1: Approximately 1.5 months after surgery and before the start of chemotherapy in the CHI group and before the start of radiotherapy in the NCH group,
- At T2: after a delay of around 6 months, within 2 weeks of the end of chemotherapy for the CHI group, or at a distance from radiotherapy for the NCH group,
- At T3: after a two-week intervention with GVS versus non-effective stimulation (known as SHAM). To assess the effect of GVS, patients will be assigned to either the effective GVS group or the SHAM group (random selection). SHAM stimulation involves using the device but receiving a very low-frequency current that has no effect on the vestibular system. This approach has already been used and validated in the COMETE unit (Caen, [name]) with which we collaborate. All cancer-free volunteer participants will undergo GVS.

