### 9.1.2 Sleep/wake cycle test

To quantify periods of activity and rest, and thus the alternation of sleep/wake rhythms, an actigraph (a watch-sized accelerometer worn on the wrist) with a sleep diary will be provided to participants 2 weeks before each assessment time (T1, T2 and T3).

The main parameters derived from the analysis of actigraphy data are the amplitude and acrophase of the activity-rest rhythm.

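### T1 and T2 fall about half a year apart, yet the tests for the secondary Axis 1 rhythm measures carry no term for season or clock time: mainly a loss of precision, and a bias if visit dates are uneven

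*Protocol*

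**What the plan says.** **Timing.** Section 8.4.4 fixes T2 for the group without chemotherapy (NCH): "T2 assessment will take place 6 months after T1". Controls (CTL) have the same rule. For the chemotherapy group (CHI) it says: "The T2 assessment will take place 2 weeks after the end of the last session of chemotherapy". Section 8.1 puts T2 at "after a delay of around 6 months, within 2 weeks of the end of chemotherapy for the CHI group", and the Table 1 column heading gives six months for everyone.

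**Measurement.** Section 8.4.2: "actigraphy data will be collected from participants 2 weeks before each assessment session (T1, T2 and T3". Section 9.1.2: "The main parameters derived from the analysis of actigraphy data are the amplitude and acrophase of the activity-rest rhythm". Section 7.1 defines "acrophase (i.e. the time of day when activity or cortisol is highest", so it is a clock time. On Axis 1 these are secondary criteria (Table 2); the main criteria there come from polysomnography. The Axis 1 hypothesis in section 6 reads: "For circadian rhythms, the sleep/wake and cortisol rhythms are expected to be less ample".

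**Analysis.** Section 12.2 compares patients with controls at T1 and at T2 by two-sample tests. For the chemotherapy effect, "the parameters of chemotherapy-treated patients will be compared between T1 and T2 by a McNemar test or a Student (or Wilcoxon) test". The alternative is a model for the T2 value adjusted for the T1 value. Section 8.1 matches on sex, age and education. Calendar date, season, day length and clock setting appear in neither the matching, the cortisol covariates listed in 9.1.4, nor any model.

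**The concern.** Activity amplitude and the clock time of peak activity may plausibly vary with daylight and with summer or winter time. At a half-year lag, the seasonal part of a woman's T2 value has the opposite sign to that of her T1 value. It therefore doubles in the difference instead of cancelling, and adjusting T2 for T1 does not remove it.

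The paired CHI test is the most exposed. It looks at one group only, so any net seasonal shift between its T1 and T2 dates would be read as an effect of chemotherapy. The patient-control comparisons are exposed in another way: controls are recruited by a separate route (8.4.1.2), and nothing keeps their visits in the same season as those of the patients they are matched to.

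**Working it through.** The protocol gives no figure to reproduce here: section 12.1 states that there is no power calculation, and no SD or effect size is given for any rhythm measure.

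**Inputs from the protocol.** T1-T2 gap six months (183 days used); two-week actigraphy windows; 25 women per group; 40 months of recruitment.

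**Assumptions not in the protocol.** Latitude 49.2 N for Caen; summer time from the last Sunday of March to the last Sunday of October; T1 dates spread evenly over the year unless stated.

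**1. Contrast within a woman.** Day length on day n is (24/π)·arccos[(sin(−0.833°) − sin φ·sin δ)/(cos φ·cos δ)], with φ = 49.2° and δ = 23.44°·sin(2π(n−80)/365.25). It runs from 8.2 to 16.2 h.

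| Gap | Mean absolute difference | Largest | Under 2 h | Different clock setting |
|---|---|---|---|---|
| 183 days | 4.9 h | 8.0 h | 18% of T1 dates | 83% |
| 152 days | 4.8 h | 7.7 h | 18% | 82% |
| 91 days | 3.5 h | 5.4 h | 22% | 50% |

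The two shorter gaps stand for an assumed range of 3 to 5 months in CHI, whose T2 follows the end of chemotherapy. CHI may thus carry a different seasonal contrast from NCH and CTL.

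**2. What remains in a group mean.** With even accrual over 40 months, the net mean T1-T2 change lies within ±0.64 h of day length and ±0.10 h of clock, whatever the starting month. The chance part for 25 women is 5.53/√25 = 1.1 h of day length and 0.912/√25 = 0.18 h of clock. If 60% or 70% of T1 visits fall in the darker half-year, the net change is 1.0 or 2.0 h of day length and 0.15 or 0.30 h of clock.

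**3. Loss of precision (illustrative).** Let season explain a share r² of variance at one visit, with opposite sign at the other, and let the rest correlate ρ = 0.6 within a woman. Its share of the variance of change is 4r² / [4r² + 2(1−r²)(1−ρ)]:
- r² = 0.02: 0.08/(0.08 + 0.784) = 9%
- r² = 0.05: 0.20/(0.20 + 0.76) = 21%
- r² = 0.10: 0.40/(0.40 + 0.72) = 36%

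**4. False positives at nominal 5% (illustrative).** Simulated t-tests with 25 women per group and 20,000 runs. The seasonal shift is assumed to be 0.25 or 0.5 SD of the change, positive for a dark-half T1 and negative otherwise.

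| T1 visits in the dark half | Shift 0.25 SD | Shift 0.5 SD |
|---|---|---|
| Paired test, 50% | 5.1% | 5.1% |
| Paired test, 60% | 5.4% | 7.2% |
| Paired test, 70% | 7.9% | 14.0% |
| Change in two groups, 70% against 50% | 6.6% | 9.8% |

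**5. Axis 2 window.** Two clock changes a year and a 14-day window give 2 × 14/365 = 7.7% of windows, or about 0.077 × 50 = 4 patients.

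**The case against.** The strongest reply is that this is noise. With recruitment over 40 months the shifts run in both directions and nearly cancel, the extra variance is already in the standard error, and the tests keep their level (5.1% above). That stands: nothing in the protocol shows uneven T1 dates, and without them the cost is precision alone. But nothing in it secures even dates either.

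It can also be said that a covariate belongs in the SAP, which is not at hand and may already deal with it. That is partly right. However, the protocol itself chooses the interval, the matching factors and the tests, and season of recruitment cannot be matched afterwards.

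Several stronger readings are tempting but not supported:
- **Every woman is measured in opposite seasons.** A T1 near an equinox gives little contrast, and the CHI interval follows chemotherapy.
- **CHI and NCH differ by season because they are recruited differently.** Both come from one cancer centre (8.3); only controls have a separate route.
- **The six-month gap causes the patient-control bias.** A comparison at one time depends on when each group was seen. For NCH against CTL, a seasonal imbalance at T1 would reverse at T2, so it could hardly imitate a cancer effect of the same sign at both visits.
- **The main criteria are compromised.** On Axis 1 rhythm is secondary. On Axis 2 it is a main criterion, but the actigraphy analysis covers the two weeks between T2 and T3. Patients are randomised to stimulation or sham, so a clock change there adds noise to that comparison, not bias.

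**Conclusion.** The point holds in a limited form. Most women will have the two rhythm recordings made under clearly different day lengths and clock settings, and the analysis stated for the secondary Axis 1 rhythm measures ignores this. Under even accrual the consequence is lost precision. Under uneven accrual, or accrual that differs between patients and controls, it is bias in the within-CHI paired test and in the patient-control comparisons.

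The 4.9 h and 83% rest only on latitude, clock rules and evenly spread T1 dates. The variance shares and error rates also rest on an assumed seasonal effect that the protocol does not supply; they show what could happen, not what will. In a study described as exploratory and without a power calculation, this is an inexpensive improvement, not a defect that undermines the trial.

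**What to change.** - **Axis 1 rhythm comparisons.** Run them as regressions that include day length computed from the visit date. For the CHI change, use the T1-T2 difference in day length.
- **Acrophase.** State in advance which clock it is read on. Express it on one fixed clock, or add a summer/winter-time term, as a sensitivity analysis, because clock setting overlaps strongly with day length.
- **Chemotherapy effect.** Compare the CHI change with the NCH change, with the same day-length term, and do not rely on the within-CHI paired test alone. The term is needed because the two groups' intervals may differ.
- **Recruitment.** Where feasible, schedule controls in the same season as the patients they are matched to.
- **Axis 2.** Handle a clock change inside the two-week window with a step term or a fixed clock. The step term is safer, since a woman who lives by local time would show an artificial one-hour step on a fixed clock.

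Visit dates will be known, so no new data are needed. The cost is one or two more covariates with 25 women per group, and some scheduling effort for controls.
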